## METHODS

### Study design and participants

We followed the CHEERS 2022 guidelines for economic evaluations (Checklist S1 in the **Online Supplementary Document**) and a trial-based CE framework [23]. The study involves two individual, parallel-arm, open-label RCTs being conducted at 31 hospitals at seven sites in six countries – three sites in Africa (Ethiopia, Nigeria, and Tanzania) and four sites in Asia (Bangladesh, two sites in India, and Pakistan) [21,22]. The study participants will be YI with low- or moderate-mortality-risk PSBI signs that seek treatment from selected hospitals in the study area and live within a catchment area where a follow-up up to day 15 can be accomplished.

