
### Statistical analysis procedures

The statistical analysis for the hospital cost data will be done in Microsoft Excel (Microsoft, Redmond, WA, USA). The data from all facilities where infants are randomised will be entered into a structured Excel document. The average costs per SYI for staff, medicines, consumables, and inpatient bed costs, will be calculated as outlined below. Mean, median, and 95% confidence intervals will be calculated using t-values per SYI receiving recommended or partial treatment for each of the cost variables at the hospital, as well as at the household level. The medical treatment costs per SYI will be the sum of the weighted average of staff costs, medicines, consumables, inpatient bed costs, and operational costs, where weights are infant-days for those receiving recommended and partial treatment. Non-medical costs on transport, food and wage loss per SYI will be added to total medical costs per SYI to estimate the total societal costs for the control and intervention arms for RCT1 and RCT2 separately. Household payments for both medical and non-medical treatment would be added to calculate the household burden in total societal costs.

The treatment outcomes for all enrolled in the control and intervention arms will be used to estimate incremental CE ratios (ICERs) for both RCTs.

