**Figure 2 F2:**
[figure not shown]
Incremental cost-effectiveness ratio quadrants.

If C_1_ < C_2_ and E_1_ > E_2_, the ICER is negative and falls in the south-east quadrant of the CE plane. In this case, the intervention is less costly and more effective, indicating that the intervention dominates the control.If C_1_ > C_2_ and E_1_ < E_2_, the ICER is negative and falls in the north-west quadrant of the CE plane. In this situation, the intervention is more costly and less effective, indicating that the control dominates the intervention.If C_1_ > C_2_ and E_1_ > E_2_, the ICER is positive and falls in the north-east quadrant of the CE plane. Here, the intervention is more costly but also more effective. The decision regarding CE depends on the CE threshold, which may vary across countries or health systems.If C_1_ < C_2_ and E_1_ < E_2_, the ICER is positive and falls in the south-west quadrant of the CE plane. In this case, the intervention is less costly but also less effective. Decisions about adoption may depend on policy considerations, such as whether a lower-cost intervention could be implemented at a larger scale to improve overall coverage and population-level effectiveness.

ICER values with negative signs are generally easier to interpret. Values in the southeast quadrant indicate that the new treatment is more effective and less costly than the existing treatment. Conversely, ICER values in the northwest quadrant indicate that the existing treatment dominates the new intervention. Positive ICER values in the southwest quadrant may suggest a cost-minimisation trade-off, but these results should be interpreted with caution, as the intervention is associated with reduced effectiveness.

In addition to ICER, we will estimate INB for each site and combined to support the interpretation of CE results [28–30]. INB are useful for quantifying uncertainty in CE, especially when differences in effectiveness are small (making ICER unstable) or when ICER results are inconclusive. For each site, incremental cost Δc = (C_1_ − C_2_) and incremental effect Δe = (E_1_ − E_2_) between intervention and control will be estimated, and INB will be calculated as λ (Δe) − Δc, where λ represents the willingness-to-pay threshold.

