### Site-wise and combined analysis plan

While site-wise analyses will provide insights into differences across study sites, results will also be presented for all sites combined and separately for the Asia and Africa regions. Variations in care pathways will be addressed through hospital-level stratification of staff, medicine, and consumable costs, using infant-days as weights to derive site averages. Costs for partial treatment will be estimated at the hospital level by using infant-days as weights for infants receiving partial treatment. Overall costs for enrolled infants will be estimated at the site level using the weighted average of those receiving recommended treatment and those receiving partial treatment. The combined average across all sites will be estimated by using enrolled infants at each site as weights for each treatment arm. The number of infants receiving at least 80% of the recommended treatment in each treatment arm will be used as weights to estimate the combined average hospital costs for the recommended treatment across all sites.

Average weighted inpatient bed costs at the site level will be estimated across all hospitals for each treatment arm using the number of SYIs enrolled in paediatric and newborn wards as weights. Combined inpatient bed costs will then be estimated using the total number of SYIs enrolled in these wards as weights at each site. Average operational costs will also be stratified at the hospital level within each site by using the number of SYIs assessed as weights, and site-stratified for combined analyses using the number of SYIs enrolled as weights at each site.

Average household costs – including registration, food, transport, and wage loss per SYI – will be calculated at the site level using the household survey sample size as the denominator. For pooled analyses, enrolled SYIs will be used as weights across sites. Both the median and the arithmetic mean will be reported to describe the distribution of costs for each variable. Uncertainty in CE will be presented using site-level, regional-level, and pooled ICERs plotted on CE planes. In addition, the mean INB will be estimated and pooled across sites, and 95% confidence intervals will be derived using the *t*-distribution based on site-level variation. An INB greater than zero will indicate that the intervention is cost-effective at the specified willingness-to-pay threshold.

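### The pooled INB interval rests only on the spread of seven site values, so it mixes sampling error with real site differences and leaves every site INB without an interval; the unit behind the hospital cost intervals is also not stated

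*Protocol article*

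**What the plan says.** All references are to the protocol article.

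- *Site-wise and combined analysis plan*, on INB: "the mean INB will be estimated and pooled across sites, and 95% confidence intervals will be derived using the" (the sentence goes on to name Student's t). As the source of variance it gives only the spread between sites: "distribution based on site-level variation". An INB above zero is then read as cost-effective; the rule does not refer to the interval.
- Same section, the only other display of uncertainty in cost-effectiveness: "Uncertainty in CE will be presented using site-level, regional-level, and pooled ICERs plotted on CE planes". On reporting levels: "results will also be presented for all sites combined and separately for the Asia and Africa regions".
- Same section, on pooled costs: "The combined average across all sites will be estimated by using enrolled infants at each site as weights for each treatment arm". No weights are stated for the pooled INB.
- *CEA*: INB is to be estimated for each site and combined, and "INB are useful for quantifying uncertainty in CE". The paragraph on presentation of costs adds that results will be read against country-specific thresholds to inform national policy.
- *Statistical analysis procedures*, on costs: "Mean, median, and 95% confidence intervals will be calculated using t-values per SYI receiving recommended or partial treatment", for each cost variable at hospital and household level. The n used is not given.
- *Study design and participants*: seven sites in six countries, three in Africa and four in Asia.

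**The concern.** The article presents INB as its tool for quantifying uncertainty, and the intended users are national decision-makers. Five of the six countries have one site, and India has two. A t-interval built on variation between sites does not exist for one site. What a country would read is therefore a point INB and a greater-than-zero rule, with nothing to show how far chance could have moved it. ICER points on a plane show how sites differ, not how uncertain each point is.

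For the pooled INB, the interval answers a question about a mean over sites like these. Site INBs may differ because effects differ, because prices differ, or because the threshold λ itself differs by country. All of this enters the interval together with sampling error and cannot be told apart from it. The trials randomise individual infants, and the information from that is used only through seven summary numbers.

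Hospital costs raise a separate issue. Staff time comes from interviews with at least 3–5 staff of each type per hospital. Medicine quantities follow the regimen, partial treatment is given a fixed duration (three days in RCT1, two after randomisation in RCT2), and ward spending is averaged. No infant-level cost variance lies behind a per-infant interval.

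**Working it through.** The article states no interval, variance or enrolment figure to reproduce. The hospital count agrees with its parts: 4 + 5 + 6 + 6 + 3 + 5 + 2 = 31.

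**1. Half-width of the planned interval.** With k sites and s the observed SD of the site INBs, half-width = t(0.975, k − 1) × s / √k.

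- All sites, k = 7: 2.447 / √7 = 0.93 s
- Asia, k = 4: 3.182 / √4 = 1.59 s
- Africa, k = 3: 4.303 / √3 = 2.48 s
- India, k = 2: 12.71 / √2 = 8.99 s
- A single site, k = 1: no interval exists

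The Asian and African figures apply only if the method is also used by region. Regional reporting implies this, but the text names INB only by site and combined. The Indian figure shows what the method would give for the one country with two sites.

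**2. What s contains.** The expected value of s² is τ² + mean(se²), where τ is the true between-site SD of INB and se is the within-site standard error. Sampling error is therefore included, and s falls as enrolment rises.

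**3. Size, under assumed inputs.** These inputs are not in the article: 500 infants per arm per site, 6% poor outcomes, λ = 1,000 USD per poor outcome averted, per-infant cost SD 40 USD, cost and effect independent.

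- se² per site = 2 × (1,000² × 0.06 × 0.94 + 40²) / 500 = 225.6 + 6.4 = 232.0, so se = 15.2 USD
- Seven sites, infant-level error only: width = 2 × 1.96 × 15.2 / √7 = 22.6 USD
- One site, infant-level error only: half-width = 1.96 × 15.2 = 29.8 USD

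Simulation of the planned interval (seven equal sites, 40,000 runs):

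| τ (USD) | Mean width (USD) | Coverage, mean over a population of sites | Coverage, these seven sites |
|---|---|---|---|
| 0 | 27.0 | 95.0% | 94.9% |
| 10 | 32.4 | 95.0% | 97.4% |
| 30 | 59.6 | 94.9% | 99.8% |
| 60 | 109.9 | 94.9% | 100% |

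With unequal sites (100 to 1,100 per arm), coverage of the mean over sites is 94.9–96.1% for an unweighted mean. It is 92.8–97.9% if the estimate is weighted by infants but its standard error is not.

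**4. Power.** If sites do not differ and an infant-level test has 90% power, the non-centrality is 1.96 + 1.28 = 3.24. A t-test on k site values with that non-centrality has power 77% (k = 7), 59% (k = 4) and 43% (k = 3).

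**5. Hospital costs.** If values from H hospitals are counted as N infants, the standard error is too small by √(N/H). RCT1 has 30 hospitals. For an assumed 500 infants per arm the factor is √(500/30) = 4.1; for 5,000 it is √(5,000/30) = 12.9. If n is the number of hospitals, the problem does not arise.

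**The case against.** The best defence is that a t-interval on site summaries is a valid and often conservative method. Each site INB carries its own sampling error, so the spread includes it, and the simulation shows close to nominal coverage for a mean across sites. That stands. A reader might infer that the planned interval ignores sampling uncertainty or does not respond to enrolment. The documents do not support this: only the multiplier t/√k is fixed, and s shrinks with more infants.

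Three other inferences go too far:

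- That all cost intervals are falsely precise. Household intervals come from real observations on at least 10% of enrolled infants per arm per site and are not affected. For hospital costs, per infant may be only the unit of expression, and the n behind the t-value is not given.
- That INB is pooled with equal site weights. The article states no INB weights at all.
- That regional INB intervals are planned. This is implied at most.

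It can also be said that bootstrap details and acceptability curves belong in a fuller analysis plan. That is fair for detail, but here the article itself names the interval method, and that method cannot produce a site interval. Using the hospital as unit also runs into few degrees of freedom, since Tanzania has two hospitals and Nigeria three. That limits the remedy for hospital costs but not for INB.

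**Conclusion.** The point holds in this form. The stated INB interval covers a mean over sites about as it should, but it confounds sampling error with differences between sites in effect, prices and threshold. It is wider than needed for the infants actually randomised when sites differ: on the assumed inputs, 60 USD against 22.6 at τ = 30, and 110 at τ = 60. Even with no site differences it costs power, 77% against 90% with seven sites.

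The more serious consequence is that no site INB has an interval, although site INBs are to be set against country thresholds. On the same inputs a single-site INB would carry a margin of about 30 USD either way that the greater-than-zero rule would not show. Enrolment, event rate, λ, cost SD and τ are all assumptions, so the USD figures are illustrative. The t multipliers depend only on the number of sites.

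For hospital costs the conclusion is conditional: if infants are counted as n, standard errors are about 4 to 13 times too small for an assumed 500 to 5,000 infants per arm. The unit and n must be stated.

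**What to change.** - Within each site and arm, bootstrap infants (clinical outcome and recommended or partial treatment status) and, separately, the surveyed households. Compute Δc, Δe and INB per site in each replicate.
- Pool the within-site differences with one common set of site weights, namely total enrolled in both arms, and state that these weights apply to the pooled INB.
- Report percentile intervals for each site and for all sites, and by region if INB is shown by region. Plot the replicates on the cost-effectiveness plane instead of single points.
- Alternatively, combine site INBs and their within-site standard errors in a random-effects model.
- Report the spread between sites separately, as heterogeneity.
- For hospital cost intervals, state the unit and n, and do not count infants as independent observations. Use the hospital as the unit, and give ranges or a sensitivity analysis where a site has only two or three hospitals.

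The cost is some scripting in place of a spreadsheet calculation. Data collection is complete, and the inputs named here (infant outcomes, treatment status, household survey) are among the data the article says are collected. Staff-time and unit-price uncertainty would still be captured only roughly, and an error common to all sites, such as an assumed partial-treatment duration, would need its own sensitivity analysis.

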## DISCUSSION

We present a detailed methodological framework for estimating the costs of managing PSBI in YIs, integrating both health system and household perspectives across different contexts. To our knowledge, we are the first to comprehensively assess both economic and clinical outcomes using such a dual-perspective approach. By analysing medical treatment costs – including staff time, medicines, consumables, inpatient bed costs, and indirect operational costs – as well as non-medical costs such as transport, food, and wage loss, our framework captures the full economic burden faced by hospitals and households. The methodology enables comparison of costs for treating low-mortality-risk PSBI in both hospital and outpatient settings, as well as moderate-mortality-risk PSBI in YIs under shorter and longer hospital stays.

By establishing a standardised approach to CEA using both ICERs and INB, and by incorporating both societal and payer perspectives, the framework supports robust evaluation of RCT outcomes. This approach strengthens evidence-based decision-making and policy formulation. The findings from this study have the potential to reshape PSBI management guidelines and support a paradigm shift in PSBI care. If outpatient treatment for YIs with low-mortality-risk PSBI signs and shorter hospital stays for moderate-mortality-risk cases are shown to be safe and cost-effective, these strategies could substantially reduce both household and health system costs while improving access to care in resource-constrained settings. Policymakers, providers, and payers would benefit from these insights.

Current WHO PSBI treatment guidelines [24] recommend seven days of hospitalisation with injectable antibiotics for YIs presenting with any sign of PSBI. However, in many low- and middle-income countries (LMICs), access to care remains limited and adherence to referral recommendations is low due to financial, logistical, or cultural barriers. Prolonged hospital stays impose a significant economic burden on families and exacerbate resource constraints for already overburdened health systems in LMICs. By integrating both economic and clinical evidence, this study contributes to the broader goal of improving neonatal survival and equity in healthcare access in resource-constrained settings. The findings will inform discussions of the WHO guideline [24] by translating trial-based costs into routine health system settings, excluding research costs and adjusting for adherence. Budget impact analyses can further estimate the financial implications of scaling up these interventions under different coverage scenarios.

### Strengths and limitations

We integrate economic and clinical evidence to identify safe, cost-efficient treatment strategies that could reduce economic burdens, inform national budgeting decisions, and potentially support revisions to WHO guidelines for improved infant care in low-resource settings worldwide.

A key strength is that the analysis is embedded within a multi-country RCT and incorporates both provider and household perspectives to assess CE from societal and provider/payer perspectives. The use of site-level stratification and INB methods further enhances transparency in quantifying uncertainty and supports decision-making using threshold-based interpretation.

Hospital cost data will be collected from all hospitals that randomise infants into treatment arms and aggregated across sites. Provider and household cost data will be collected over a consistent, recent financial period, ensuring alignment of price inputs and minimising variability due to inflation or exchange rate fluctuations during the multi-year enrolment period. Household expenditures will be collected close to the time of care (day eight, 15, or within two weeks after the 15-day outcome visit), with cross-verification against receipts or facility records where available, thereby reducing recall bias. Provider cost and outcome analyses will include the full randomised cohort, strengthening the robustness of the primary CE estimates.

One limitation is that household costs and wage data will be collected during the final nine months of the study using a purposive sample of approximately 10–15% of enrolled infants in each treatment arm at each site. Although this improves operational feasibility, it may introduce selection bias when estimating non-medical costs if respondents differ systematically from those not interviewed. No imputation or adjustment methods will be applied; although missing data are assumed to be random, non-random patterns cannot be entirely ruled out.

The analysis does not account for broader health system constraints, implementation barriers, capacity limitations, or informal healthcare costs that families may incur. The impact inventory focuses on direct effects within the healthcare sector and does not include impacts on other sectors. Factors such as supply chain inefficiencies and quality-of-care metrics specific to PSBI treatment are also outside the scope of this framework. In addition, research-related costs, including staff time for outcome assessment, monitoring and supervision, and protocol-specific training, will not be included.

The study period varies across hospitals and sites. While outcome data will be collected throughout the study, cost data will be collected during the final nine months. Although this may raise concerns regarding representativeness and recall bias, all cost data will be collected in local currency using a consistent price year, ensuring that salaries, medicine prices, and other treatment cost components remain constant for the defined price year.

Despite these limitations, this framework provides robust and policy-relevant evidence for evaluating cost-effective strategies to improve the management of PSBI in YIs in resource-constrained settings.

## CONCLUSIONS

This study presents a comprehensive methodological framework for evaluating the cost-effectiveness of alternative treatment strategies for PSBI in YI across Asia and Africa. By integrating both health system and household perspectives, the framework captures the broader economic implications of outpatient treatment and shorter hospitalisation strategies in resource-constrained settings. The use of standardised costing methods, ICER and incremental net benefit approaches, and multi-country randomised trial data strengthens the robustness and policy relevance of the analysis. Findings from this work will support evidence-based decisions for optimising PSBI management and may contribute to future revisions of WHO guidelines to improve access, affordability, and neonatal outcomes globally.

## Additional material

Online Supplementary Document
